#### Secondary outcomes

A detailed description of all the secondary outcomes is shown in Table 2. They will include validated questionnaires and tests for evaluating: (a) musculoskeletal pain [41] (intensity, frequency, and interference) of the low back, neck, shoulders and hands/wrists; (b) psycho-affective state [42–46] (subjective happiness, anxiety and depression, burnout, sleep quality, and quality of life) which will be collected by a self-administered written questionnaire; (c) work-related variables [47–49] (work ability, performance, physical exertion, and absenteeism) which will be obtained by a self-administered written questionnaire and from the official registry of the participating eldercare institution; and (d) physical fitness (trunk, lower and upper limbs muscle performance), which will be evaluated by a battery of physical performance tests [50–52] previously validated by our research group to be carried out remotely by real-time videoconference [53]. The participant's self-reported days of medication consumption of analgesics and hypnotics/anxiolytics during the last 7 days at each assessment point will also be recorded.

### Adverse events

Adverse events occurring during the supervised exercise sessions will be collected by the professional supervising the sessions and divided into 2 types: a) technical (connection and/or operation problems with the videoconferencing system) and b) participant safety-related (pain, discomfort, or any other health-related problem appearing during the session). Adverse events will also be classified as minor (those that slightly hinder the development of the exercise session) and major (those that prevent the development of the exercise session).

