Telerehabilitation is an increasingly used alternative for remotely delivering health services using telecommunications technologies [21, 22]. Although previous studies reported some positive effects on pain and other health-related outcomes, a recent review stated that it is imperative to conduct high quality clinical trials in order to identify effective telerehabilitation interventions [21]. To the knowledge of the authors, the great majority of internet-based interventions have consisted of websites with content for autonomous consultation, or individual home-videoconference sessions [21–25]. There are two positive experiences showing that synchronous supervised sessions are a feasible way to present group therapeutic exercise interventions in people with chronic obstructive pulmonary disease [26] and older adults [27], but no study has been addressed to assess their effectiveness on musculoskeletal disorders yet. Synchronous supervision and group dynamic could be important for designing exercise programs, as both features are related to higher participant adherence, what may therefore lead to a higher effectiveness [28, 29]. In addition, it could also allow for greater intervention safety, since participants can be continuously monitored for correct execution during exercising.

Thus, a study protocol for a randomized controlled trial was designed with the aim of assessing the effects of a videoconference-based group therapeutic exercise intervention in the medium and long term on the musculoskeletal pain of eldercare workers. Secondary outcomes will include measures related to the psycho-affective state, work-related variables and physical fitness.

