### Control group

Participants in the control group will not receive any intervention and will be instructed to continue with their usual lifestyle.

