### Experimental group

#### Supervised phase

Participants in the experimental group will take part in a 12-week exercise intervention, consisting of two videoconference-supervised sessions per week of 45 min each. A minimum interval of 48 h will be ensured between sessions. The sessions will be carried out in groups of a maximum of 10 participants, implemented in the workplace but outside of working hours, and remotely supervised in real-time by a professional with previous experience in delivering group exercise sessions. Real-time videoconference platforms such as Webex (Cisco Systems, Milpitas, USA) will be used, and audio and video will be continuously shared between participants and trainer to allow complete bidirectional feedback (Fig. 2).

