#### Unsupervised phase

When the 12-week supervised sessions are finished, participants in the experimental group will be encouraged to continue performing 2 weekly sessions on their own until the 48-week follow-up. To facilitate this autonomous training, we will create supportive material for the sessions that will include two 45-min recordings with the equivalent content to a session planned for the 12^th^ week, explanatory videos of the 9 exercises performed in the supervised program and their corresponding progressions, as well as written instructions about how to perform the exercises. To record completion in this unsupervised phase, participants will be asked, every 12 weeks and until the 48-week assessments (Fig. 1), the following questions: (a) in the last 12 weeks, in how many weeks did you perform the exercises? (0–12) and (b) on average, in each of those weeks in which you performed the exercises, on how many days did you perform them? (0–7). The result of the multiplication of both answers will be considered the number of performed unsupervised sessions. In this case, self-reported completion will be calculated as a percentage of performed sessions (i.e., 72 sessions = 100% completion in the unsupervised phase).

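### Adverse event collection, definition and grading are tied to supervised sessions, so event rates cannot be compared between arms or described for the 36-week home phase

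*Protocol article*

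**What the plan says.** The Adverse events section is the only text on the subject in the protocol article. It sets three limits.

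- **Collection:** "Adverse events occurring during the supervised exercise sessions will be collected by the professional supervising the sessions".
- **Definition:** events are either technical or "participant safety-related (pain, discomfort, or any other health-related problem appearing during the session").
- **Grade:** events of both types are also minor or major, and a major event is "major (those that prevent the development of the exercise session"). Minor events are those that hinder the session slightly.

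The supervised phase is a "12-week exercise intervention, consisting of two videoconference-supervised sessions per week of 45 min each". After it, "participants in the experimental group will be encouraged to continue performing 2 weekly sessions on their own until the 48-week follow-up". During that phase the article describes two questions every 12 weeks, both about how many sessions were done. Of the other arm, the Control group section says: "Participants in the control group will not receive any intervention and will be instructed to continue with their usual lifestyle".

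Outcomes are assessed at baseline, 12 and 48 weeks with no restriction by arm (Study design). Table 2 includes pain intensity, frequency and interference at four sites, analgesic days, and absenteeism with its reason.

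**The concern.** A rule that needs a supervised session, both to observe an event and to grade it, cannot work where there is no session. That excludes the whole control arm, problems that emerge after a session ends, and everything in the home phase. The home phase is where live monitoring has stopped, while the recordings supplied match a week-12 session, the last step of the progression scheme.

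Two things are at stake. First, there is no comparator for adverse events, so the count in the exercise arm cannot be set against a background rate in workers with physically demanding jobs. Second, a low count would partly reflect the narrow collection window. The article presents the programme as a candidate for wide workplace use, and adopters would want comparative adverse event rates beside the benefit estimates.

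The grade has its own weakness. It measures disruption to the session, so a health problem that barely interrupts the session is minor whatever follows from it.

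**Working it through.** **Inputs.** Supervised phase: 12 weeks, 2 sessions per week, 45 min each (Supervised phase). Final follow-up: week 48. Unsupervised phase: 2 sessions per week advised, with 72 sessions counted as full completion (Unsupervised phase). Recall periods and pain sites: Table 2 and its footnote.

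**The plan's own session counts.**
- Supervised: 12 × 2 = 24, as stated.
- Unsupervised: (48 − 12) × 2 = 36 × 2 = 72, as stated.

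**Share outside adverse event collection, exercise arm.**
- Sessions: 72 / (24 + 72) = 72/96 = 75%.
- Weeks: 36/48 = 75%.

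**Share covered within the supervised phase.**
- Session time per participant: 24 × 45 min = 1,080 min = 18 hours.
- Hours in 12 weeks: 12 × 168 = 2,016.
- 18 / 2,016 = 0.9%.

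**Both arms together.** There are 2 × 48 = 96 arm-weeks. Those with any adverse event collection number at most 12, all in the exercise arm: 12/96 = 12.5%. For controls the figure is 0 of 48.

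**What the other outcomes can show.**
- *Pain and analgesic use* look back 7 days. The two post-baseline assessments cover about 2 of 48 weeks: 2/48 = 4%. A flare that resolved in between is not seen.
- *Pain sites* are low back, neck, shoulders and hands/wrists. No lower-limb site is listed, although Table 1 schedules squats, reverse lunges and glute bridges.
- *Absenteeism* looks back one year. Taking a year as 52 weeks, the week-12 answer covers 12 trial weeks and 52 − 12 = 40 earlier weeks. The week-48 answer covers all 48 trial weeks, with the two phases merged. An injury that caused no absence does not appear.
- None of these is recorded as an adverse event, and continuous outcomes are compared as group means, where an average benefit can mask injury in a few people.

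**The case against.** **The trial is not without harm data.** A reader might infer from the adverse event text that nothing about harm is known for controls or for the home phase. The article does not support that. Pain, analgesic use and absenteeism with reason are assessed in both arms at 12 and 48 weeks, and the one-year absence question at week 48 spans the whole home phase. This objection stands.

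**Musculoskeletal harm can be compared in part.** It would also be too strong to say that the trial cannot tell whether the programme worsens musculoskeletal pain. Low back pain is the primary outcome and is compared between arms at both times; a net worsening at any of the four sites would show. This stands too. What cannot be compared is the rate of discrete events.

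**The safety remark in the Introduction is modest.** It says of synchronous supervision that "it could also allow for greater intervention safety", and it concerns monitoring during live sessions. It claims nothing for the home phase, so there is no contradiction with the collection rule.

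**Technical and safety events are already separated.** A lost connection would be a major technical event and need not be mixed with injuries. Only the shared grading criterion remains open to criticism.

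**The article is condensed.** It nowhere states that no other route of reporting exists, and a fuller document may add one. That limits the claim to what is described. It does not remove the point, because the session-bound definition and grade are fixed in the text.

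**The 72 home sessions are advised.** The 75% describes planned exposure; actual exposure depends on completion.

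**Conclusion.** The point holds in limited form. Under the rule as written, no adverse event data are described for controls, for time between sessions, or for 36 of the 48 weeks in the exercise arm (72 of 96 advised sessions, 75%). The remaining outcomes give indirect evidence in both arms. They would miss transient flares, injuries without absence and lower-limb problems, so they do not substitute for comparable event rates.

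This rests on two assumptions: that the Adverse events section is the whole collection rule, which is inferred from the absence of any other provision, and that home sessions are done as advised, for the session share only. The primary efficacy estimate does not change. The change is worth making because recruitment is still active and the contacts needed already exist.

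**What to change.** 1. Add one identical adverse event item for both arms at the existing 12- and 48-week assessments: any new injury, pain flare or other health problem since the last assessment, and whether care was sought. Missed work need not be asked again, since absenteeism already covers it.
2. Base the between-arm comparison of adverse events on that item alone, reported by arm and by phase.
3. If a harm question is added to the exercise arm's 12-weekly contacts, report it descriptively only, or ask both arms on the same schedule. Asking one arm more often and with shorter recall (12 against 36 weeks) would tend to raise its count.
4. Keep supervisor recording in sessions and the planned technical/safety split. Grade participant-safety events by their consequence for the participant instead of by session disruption.

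**Cost.** One questionnaire item and a short amendment. Recall is long at the second assessment (48 − 12 = 36 weeks), so mild events will be under-reported in both arms. For participants already enrolled, events before the change can only be reported retrospectively.

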**Fig. 2 Fig2:**
[figure not shown]
Setting up of the videoconference-supervised exercise sessions. *Legend*: **A** workplace setting in a participating nursing home; **B** setting of the professional supervising the session; **C** screenshot of a videoconference session

The technical content of the program is based on a literature review, authors’ expertise and field experience, as well as on the results of a previous pilot trial that we carried out between January and March 2020 with 20 eldercare workers [33], that allowed us to define the exercises, intensities, and feasibility of a program addressed for reducing the musculoskeletal pain in this population. Intervention details are reported based on the Template for Intervention Description and Replication (TIDieR) Checklist [34]. Sessions will start with a warm-up (5–10 min), including joint mobility and aerobic activation exercises focused on increasing heart rate. The main part of the session will consist of resistance exercises (30 min) performed at moderate-high intensity. In total, 9 exercises will be performed throughout the program (Fig. 3). In each session, 4 sets of 6 resistance exercises will be performed, with a 2-min active rest (dynamic stretching and breathing exercises) between sets. Exercises will be systematically varied between sessions so that each of them is evenly performed during the program. In each set, exercises for the different major muscle groups will be alternated in a circuit manner (e.g., lower limb, upper limb, trunk, lower limb, upper limb, trunk) (Table 1). Unilateral exercises will be alternated between sets so that both sides of the body are evenly worked in each session. Exercises will be performed with minimal equipment, combining body-weight and 2-m-long elastic band exercises. Three progression levels will be set for each of the exercises: progression 1 (weeks 1–4), progression 2 (weeks 5–8) and progression 3 (weeks 9–12) (Fig. 3). All participants will start in progression 1, and transition to a subsequent progression will only be allowed if the participant completes ≥ 4 sessions in the previous progression level. Progression levels are achieved by modifying the exercise technique (e.g., increasing the force lever) or utilizing elastic bands of different resistances (1.7, 2.1 and 2.6 kg at 100% elongation for progressions 1, 2 and 3, respectively) (Fig. 3). One minute will be dedicated to the completion of each exercise (including work and rest times), and within each progression level, the work:rest ratio will augment from 30:30 to 45:15 s, thus adding 5 s of work and reducing 5 s of rest each week (Fig. 4). Participants will be asked and monitored to work at a rate of perceived exertion between 3 (moderate) and 5 (strong) on the Borg's CR-10 scale [35] and not to reach failure in any of the exercises. If any of the exercises cause intolerable pain, the 4-stage exercise adjustment model proposed by Jakobsen et al. [36] will be used: (1) reduce loading intensity (e.g., returning to a previous progression level or even performing the exercise without external resistance), (2) reduce movement velocity, (3) reduce range of motion, and (4) interrupt exercise. If an exercise needs to be interrupted, it will be replaced by a pain-free exercise focused on the same muscle group. Sessions will finish with a cool-down (5–10 min), including static stretching and breathing/relaxing exercises. Daily attendance will be recorded by the professional who supervises the sessions. This professional will also collect information on the completion and intensity of each participant's training in each session. Adherence will be reported as the percentage of sessions in which participants performed the planned training regarding completion and intensity (i.e., 24 sessions = 100% of adherence) [37].

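### The minor/major grade for adverse events measures disruption of the exercise session, so within safety-related events it does not reflect harm to the participant

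*Protocol article*

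**What the plan says.** The Adverse events section of the protocol article describes what the session supervisor collects during supervised sessions, on two axes.

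- **Type.** Events are either "technical (connection and/or operation problems with the videoconferencing system") or "participant safety-related (pain, discomfort, or any other health-related problem appearing during the session").
- **Grade.** Events of both types are also "classified as minor (those that slightly hinder the development of the exercise session) and major (those that prevent the development of the exercise session").

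The article prints no other grade for adverse events.

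Two statements under Experimental group, Supervised phase, determine how this rule works in practice. The first is the pain procedure: "If any of the exercises cause intolerable pain, the 4-stage exercise adjustment model" applies, and its last stage is to interrupt the exercise. The text continues: "If an exercise needs to be interrupted, it will be replaced by a pain-free exercise focused on the same muscle group". The second is the format: "The sessions will be carried out in groups of a maximum of 10 participants".

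**The concern.** Readers of a trial report will take a major safety-related event to be one that did the participant substantial harm. The printed rule does not ask about harm. It asks what happened to the session. The two can diverge in either direction, and the pain procedure makes the divergence foreseeable, because it is designed to keep the session going when an exercise has become intolerable.

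At stake is what the trial can conclude about harm. The Introduction suggests, tentatively, that real-time supervision may make the intervention safer. A report of no major safety-related events would look like support for that idea. Under this rule it would show only that no such event prevented a session.

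**Working it through.** No arithmetic applies, and the plan gives no figure to reproduce. The check is to apply the printed rule to a set of events, reading it together with the replacement rule and the group format. Because the article does not define the unit, each event is graded under both readings of the word session.

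| Event | Type | Grade if the session is the group's | Grade if the session is the individual's |
|---|---|---|---|
| Brief connection problem, session resumes | Technical | Minor | Minor |
| Connection failure that prevents the session | Technical | Major | Major |
| Intolerable pain; exercise interrupted and replaced; session continues | Safety-related | Not major | Not major |
| Complaint that barely disturbs the session; later health care or work absence | Safety-related | Minor | Minor |
| Injury removes one participant; the others continue | Safety-related | Not major | Can be major |
| Session substantially curtailed but not prevented | Either | No grade fits | No grade fits |
| Health problem that prevents the session | Safety-related | Major | Major |

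Four things follow.

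1. **Pain that stops an exercise.** The replacement rule means that the participant carries on with another exercise. Neither the group's session nor that person's session is prevented, so the event is not major under either reading, provided that the session does continue.
2. **Delayed consequences.** The rule looks only at the session. What happens to the participant afterwards cannot change the grade.
3. **A gap between the grades.** The lower grade requires slight hindrance and the upper grade requires prevention. Anything between them has no place.
4. **An undefined unit.** With up to 10 people in a session, an injury that ends one person's participation gets a different grade depending on the reading. Two supervisors could grade the same event differently and both follow the text.

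**The case against.** The strongest case on the other side has five parts.

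- **The types are already separated.** This stands. A cancelled videoconference would be recorded as technical and major, and pain as safety-related. A reader might infer that connection faults will be counted together with injuries, or that any lost connection is major. The article supports neither: the type axis keeps the two apart, and a connection fault is major only if it prevents the session. But separation by type does not repair the grade within the safety-related type.
- **The individual reading is available.** This also stands. The Supervised phase section has the supervisor record each participant's completion and intensity per session, and adherence is counted per participant out of 24 sessions. A reader might infer that an injury to one member of a group can never be major. That holds only under the group reading, which the article does not state. What remains is an ambiguity.
- **Consequences are measured elsewhere.** In part. Table 2 includes pain at four body sites, days of analgesic use, and absenteeism with its reason, and outcomes are assessed at baseline, 12 and 48 weeks. These are outcome measures and do not grade events.
- **The article is a condensed protocol, and safety is not among its stated outcomes.** The full protocol may hold a harm-based grade, and its absence here would not by itself be a finding. The point concerns the rule that the article does print, which covers safety-related events explicitly.
- **The article does not call the grade severity.** True, but minor and major adverse events will be read that way.

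**Conclusion.** The point holds in this form: the minor/major grade rests only on disruption of the session, for both event types, so grades among safety-related events do not track harm. Intolerable pain that stops an exercise is not major if the session continues, a complaint with later consequences can be minor, events between the two definitions are ungraded, and the unit of the session is left open.

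No numerical size can be given. The article gives no rates for connection failures or for interrupted exercises, and the conclusion does not depend on any. It rests on two assumptions: that the replacement rule is followed as written, and that no harm-based grade in the full protocol takes precedence over the printed one.

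The primary outcome and its analysis are not affected. What is affected is any statement about harm that relies on the grade. The change should be made, although the trial can answer its main question without it.

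**What to change.** Keep the session-disruption scale for technical events only, and report it as feasibility. For that scale, state whether the session is the group's or the individual's, and define a grade for events that curtail a session without preventing it.

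Classify safety-related events by consequence for the participant, for example:

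- no change to the session;
- exercise adjusted or interrupted under the existing adjustment model;
- withdrawal from the session or the programme;
- health-care contact or work absence.

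Report the number of participants and the number of events in each class. This changes only how events are recorded and reported; the handling of pain during sessions stays as it is. If the full protocol already contains a harm-based grade, name that grade as the one to be reported.

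The cost is one extra field on the log that the supervisor already keeps for each participant and session, plus a follow-up question at the next session about what came of the event. The Trial status section says that the first participants are already in the intervention and recruitment is still open, so later events can be classified as they occur. Events already logged can be regraded only as far as the recorded information allows, and the report should say how many could not be.
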